### Interim analyses {21b}

The data and safety monitoring committee will be responsible for monitoring the safety and efficacy of this study and is authorized to make decisions regarding the termination of the trial.

### Methods for additional analyses (e.g., subgroup analyses) {20b}

This study will pre-specify subgroups for the comparison of treatment effects. These subgroups are based on known factors that may influence treatment outcomes in gout patients, including patient age, prior treatments, and the severity of gout.

### Methods in analysis to handle protocol non-adherence and any statistical methods to handle missing data {20c}

In this study, intention-to-treat (ITT) analysis will be employed to assess the trial policy regarding the treatment received by allocated participants, while per-protocol (PP) analysis will be utilized to exclude or scrutinize participants deviating from the treatment protocol. This study anticipates minimal or no occurrence of missing outcome data, as the trial will not be terminated before all data is collected.

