#### Criteria for discontinuing or modifying allocated interventions {11b}

Adverse events: If a participant experiences severe adverse events or side effects directly attributed to the allocated intervention, the intervention may be discontinued or modified as necessary for the participant’s safety. The decision will be based on clinical judgment and in consultation with the study’s principal investigator and relevant medical professionals.Participant withdrawal of consent.The participant fails to comply with the study requirements or guidelines related to the allocated intervention.Changes in the participant’s health status or external factors affecting the study may warrant modification or discontinuation of the allocated intervention.

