### Sample size {14}

The sample size was calculated using GPower. This study is a randomized controlled trial with an equal number of subjects in the intervention and control groups. The primary outcome measure was the serum uric acid concentration. According to previous studies [21], the serum uric acid concentration of patients in the control group was 420 ± 100 µmol/L. The effect size was set to 0.25, bilateral *α* = 0.05 was set, and the power was 80%; at least 14 patients will be included in each group, making the sample size *N* = 28. Considering a 10% follow-up dropout rate, at least 30 patients will be included, with a minimum of 15 patients in each group.

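### The protocol's sections on dropout, exclusions and ITT contradict each other, so the analysis called ITT would be completers-only

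*Protocol article*

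**What the plan says.** Three sections of the protocol article bear on patients without complete outcome data.

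- **Sample size {14}:** "at least 14 patients will be included in each group, making the sample size *N* = 28". Then: "Considering a 10% follow-up dropout rate, at least 30 patients will be included", with 15 per group.
- **Statistical methods for primary and secondary outcomes {20a}:** outcomes go into a two-way repeated measures ANOVA. Patients who cannot finish for reasons beyond control, or who come to breach an entry criterion while on study, are left out of the analysis. No analysis set is named for this rule.
- **Missing-data section {20c}:** both an ITT and a per-protocol analysis are named, and the per-protocol analysis deals with deviators. On missing outcomes the section says: "This study anticipates minimal or no occurrence of missing outcome data, as the trial will not be terminated before all data is collected".

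Other sections foresee loss. The criteria for discontinuing or modifying interventions {11b} list withdrawal of consent and also "The participant fails to comply with the study requirements or guidelines related to the allocated intervention". Adverse event reporting {22} has patients withdrawn from the trial after an intervention-related adverse event. Interim analyses {21b} gives a committee authority to terminate the trial.

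**The concern.** The planning figure and the analysis section describe the same follow-up differently, and the reason offered in {20c} is about the trial as a whole rather than the patient. The exclusion rule in {20a} then settles what happens to the patients who are lost: they leave the analysis. An ITT analysis is meant to keep every randomised patient in the arm assigned, so {20a} and {20c} cannot both apply to the same analysis.

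This matters because loss in this trial could plausibly depend on arm and on outcome. Only the researchers who assess patients and collect data are blinded {17a}. The Background {6a} describes gout patients as prone to give up exercise for fear of pain, and the Discussion expects ice to improve adherence by easing symptoms. If that is right, those who stay may differ between arms, and a completers-only comparison of serum uric acid (SUA) or BMI need not estimate the effect in all randomised patients.

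The second limb of the exclusion rule adds to this. BMI of at least 25 is an entry criterion and BMI is a primary outcome. Read literally, a patient whose BMI falls below 25 on study could be excluded because of the outcome itself.

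**Working it through.** **Inputs from Sample size {14}:** "The effect size was set to 0.25"; "bilateral *α* = 0.05 was set"; power 80%; SUA SD 100 µmol/L ("the serum uric acid concentration of patients in the control group was 420 ± 100 µmol/L"); 28 evaluable; 10% dropout; 30 enrolled. Three visits (0, 4, 12 weeks) come from Outcomes {12}.

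**1. The plan's own N.** Take 0.25 as Cohen's f for the group-by-time interaction, with 2 groups and m = 3 visits. The correlation between visits (ρ = 0.5) and sphericity are assumptions, since the protocol gives neither.
- λ = f² × N × m / (1 − ρ) = 0.0625 × 28 × 3 / 0.5 = 10.5, on 2 and 52 degrees of freedom.
- Power is 0.812 at N = 28 and 0.778 at N = 26, so 28 is reproduced.
- For ρ from 0.3 to 0.7 the required N runs from 38 down to 18.

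**2. What 10% dropout means.**
- Expected loss: 30 × 0.10 = 3, leaving 27 completers against 28 required.
- Full inflation: 28 / 0.9 = 31.1, or 32 with equal arms. Enrolling 30 absorbs 2/30 = 6.7%.
- Power with 27 completers at ρ = 0.5 is 0.795 against 0.812 with 28. The loss of power is small; the issue is which patients are analysed.

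**3. How likely is no missing data?** Binomial(30, 0.10), assuming independent losses:
- P(none missing) = 0.9³⁰ = 0.042
- P(at least 2) = 0.816
- P(at least 3) = 0.589

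**4. The three sections side by side.**

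| Section | Expected loss | Fate of those lost |
|---|---|---|
| {14} | 10%, 3 of 30 | allowed for by enrolling 2 extra |
| {20a} | foreseen | left out, no analysis set named |
| {20c} | minimal or none | ITT named, so kept |

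**5. Possible size of bias (assumed scenario).** Suppose k of 15 patients are lost in one arm only, and their unseen SUA differs from that arm's completers by δ. Completers-only analysis then shifts the between-arm difference by (k/15) × δ.

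| k | δ = 50 µmol/L (0.5 SD) | δ = 100 µmol/L (1 SD) |
|---|---|---|
| 2 | 6.7 | 13.3 |
| 3 | 10 | 20 |

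For scale, the standard error of an unadjusted comparison at one visit is 100 × √(2/15) = 36.5 µmol/L. The shift is therefore 6.7/36.5 = 0.18 to 20/36.5 = 0.55 standard errors.

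**The case against.** A reader might infer that the ITT analysis has no stated handling of missing patients at all. The document does not support that: {20a} does state a rule, exclusion. The defect is that this rule conflicts with ITT. Nor is the absence of an imputation model or a detailed sensitivity plan a finding, since those can sit in an analysis plan that is not shown.

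The strongest defence of the text has four parts.

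- **The 10% may be a safety margin.** An allowance can exceed the loss that is really expected, and the protocol has retention measures: a transport subsidy {11c} and reminders {18b}. This softens the clash between {14} and {20c}, but it does not rescue the reason given in {20c}.
- **The exclusion in {20a} may be meant for the per-protocol set.** That would remove the conflict. But the rule stands in the section on primary and secondary outcomes, without that limit.
- **The discontinuation criteria {11b} concern the intervention.** Stopping treatment is not the same as losing outcome data, so the non-compliance item is weak evidence of missingness. Withdrawal of consent in {11b} and withdrawal from the trial in {22} are better evidence.
- **The bias figures are modest and assumed.** This is correct. They need all losses in one arm and a 0.5 to 1 SD difference, neither of which is in the protocol, and the standard error is for a single visit rather than the planned repeated-measures test. The trial also calls itself exploratory {8}.

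**Conclusion.** The point holds as a contradiction among {14}, {20a} and {20c}. The arithmetic on the protocol's own 10% is firm: 3 of 30 expected missing and 27 completers against 28 required. The 4.2% chance of complete follow-up also assumes independent losses. The justification in {20c} does not follow, and it sits badly with the provisions for withdrawal in {11b} and {22} and for termination in {21b}.

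Followed as written, the plan would label a completers-only result ITT. Whether that result would be biased, and in which direction, cannot be known from the document. The 7 to 20 µmol/L range illustrates what loss in one arm could do; it is not an estimate. The matter should be settled before analysis, since it affects both primary outcomes, but it does not call for a change in design.

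**What to change.** 1. In {20c}, delete the sentence expecting minimal or no missing data, with its reason, and carry over the planning figure from {14}: about 10%, or 3 of 30.
2. In {20a}, state that the exclusion of non-completers and of patients who come to breach entry criteria applies to the per-protocol set only. Changing {20c} alone would leave the conflict in place.
3. State that the ITT analysis of SUA and BMI keeps all randomised patients in their assigned arm under missing-at-random. One option is a mixed model for repeated measures using all available visits, in place of a repeated measures ANOVA restricted to patients with every visit. Multiple imputation is another.
4. Add a simple missing-not-at-random sensitivity analysis, for example shifting the unseen values in each arm separately. Its details can be left to the analysis plan.
5. Report missingness by arm, visit and reason.

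The cost is a paragraph of wording and a little extra analysis, with no more patients or visits. The interval may be slightly wider, to reflect the missing data.

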### Plans to give access to the full protocol, participant-level data, and statistical code {31c}

All data relevant to the trial will be made publicly accessible following reasonable requests upon the completion of the trial.

## Oversight and monitoring

### Composition of the coordinating center and trial steering committee {5d}

The trial steering committee will consist of an experienced clinical expert in gout and an exercise rehabilitation expert. They will serve as an independent team to oversee the conduct of the trial.

### Composition of the data monitoring committee, its role, and reporting structure {21a}

The data monitoring committee is composed of an exercise rehabilitation expert and a statistician who are independent and free from any conflicts of interest. They are responsible for scrutinizing the integrity and safety of the data.

### Adverse event reporting and harms {22}

Due to the intervention being safe and non-invasive, there is a lower risk of developing adverse events in this study. Patients will be withdrawn from the trial if they experience any adverse event related to the intervention, such as exercise injuries, falls, chest pain, dyspnea, or hypoglycemia. Furthermore, all adverse events will be recorded and reported in the study results.

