## Statistical methods

### Statistical methods for primary and secondary outcomes {20a}

All data will be analyzed using SPSS version 29. One-way ANOVA will be used to evaluate whether there were significant differences in age, gender, and symptom severity of gout between the intervention and control groups. Two-way repeated measures ANOVA will be used to analyze differences in outcomes before and after treatment. The significance level will be set at *p* < 0.05. If some patients are unable to complete the experiment due to uncontrollable factors or if they violate the inclusion criteria during the study, these patients will be excluded from the analysis.

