### Plans for communicating important protocol amendments to relevant parties (e.g., trial participants, ethical committees) {25}

All revisions to the protocol require approval from the Human Research Ethics Committee at USM. Once the revised protocol is approved, we will inform the participants and the involved researchers. We will also revise and update the protocol in the clinical trial registry. Any deviations from the protocol will be fully documented using a breach report form and submitted to Human Research Ethics Committee at USM.

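### A related adverse event means leaving the trial in section {22} but only an optional stop or change of the intervention in section {11b}; read plainly, {22} may also end outcome measurement for harmed patients

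*Protocol article*

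**What the plan says.** Two sections of the protocol article tell staff what to do after an adverse event caused by the intervention.

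- Adverse event reporting and harms {22}: "Patients will be withdrawn from the trial if they experience any adverse event related to the intervention". The examples are falls, injuries during exercise, hypoglycemia, chest pain and dyspnea. The section also promises that all adverse events will be recorded and reported.
- Criteria for discontinuing or modifying allocated interventions {11b}: "If a participant experiences severe adverse events or side effects directly attributed to the allocated intervention, the intervention may be discontinued or modified". The decision rests on clinical judgment, in consultation with the principal investigator and relevant medical professionals.

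Three other sections bear on what happens to the data.

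- Section {20c}: "intention-to-treat (ITT) analysis will be employed to assess the trial policy", with a per-protocol analysis alongside, and "This study anticipates minimal or no occurrence of missing outcome data". The reason given is that the trial will run until data collection is finished.
- Section {20a} names two grounds for removal, failure to finish for reasons outside anyone's control and a later breach of eligibility, and rules for both that "these patients will be excluded from the analysis".
- Sample size {14}: 14 per group, 28 in total, then "Considering a 10% follow-up dropout rate, at least 30 patients will be included".

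Outcomes are measured at weeks 0, 4 and 12 (Outcomes {12}), and the sessions run for 4 weeks (Intervention description {11a}). The rate of gout flare is a secondary outcome, listed as an adverse effect.

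**The concern.** Staff facing a severe related event, or a side effect attributed to the intervention, have two instructions that cannot both be followed. A clinician who modifies the sessions under {11b} departs from {22}, and section {25} requires deviations to be documented on a breach report form.

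The statistical stake is what happens afterwards. If withdrawal from the trial is taken at its word, the patient makes no further visits. The values lost would be those of patients harmed by the intervention, which is not a random subset, and an intention-to-treat analysis cannot use measurements that were never taken. The flare outcome would be affected too: a flare judged to be related falls under the rule in {22}, so the event being counted could end the counting. No analysis plan can repair this later, because {22} is a rule of conduct.

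**Working it through.** The point is mainly textual, so the rules are set side by side first.

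| | Section {22} | Section {11b} |
|---|---|---|
| Trigger | any adverse event related to the intervention | severe adverse events, or side effects directly attributed to the intervention |
| Force | mandatory (*will*) | discretionary (*may*) |
| What ends or changes | participation in the trial | the intervention |

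1. **Overlap.** *Any* in {22} includes severe related events and attributed side effects, so both rules apply to these and prescribe different actions. Whether a mild related event also falls under {11b} depends on how broadly side effects is read.

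2. **Reconciliation.** No section gives one rule priority. Section {11b} shows that the article can speak of stopping the intervention alone; {22} names the trial.

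3. **Effect on measurements.** No section says that visits stop after withdrawal, and none says that they continue. The reporting promise in {22} covers the adverse events themselves, not serum uric acid, BMI, pain or the other outcomes. The reason in {20c} for expecting few missing data concerns the trial as a whole, not a patient whom {22} removes.

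4. **Timing.** Sessions end at week 4. An event arising in a session therefore comes before both post-baseline visits, and a patient who then leaves contributes baseline values only.

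5. **The plan's own sample size.** Section {14} gives effect size 0.25, two-sided α = 0.05 and power 80%. Taking 0.25 as Cohen's f for the group-by-time interaction, with k = 2 groups, m = 3 times, and correlation ρ = 0.5 and sphericity assumed because the article states neither:
 - λ = f²·N·m/(1 − ρ), with df = (k − 1)(m − 1) and (N − k)(m − 1).
 - N = 28: λ = 0.0625 × 28 × 3 / 0.5 = 10.5, df 2 and 52, power 0.812.
 - N = 26: λ = 9.75, df 2 and 48, power 0.778.
 - The stated 28 is reproduced.

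6. **Margin for losses.** 30 − 28 = 2 patients, or 2/30 = 6.7%, for all causes together. The stated 10% dropout would be 3 patients, leaving 30 × 0.90 = 27. Each patient lost is 1/15 = 6.7% of an arm.

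7. **Power along the way.** Under the model in step 5, power is 0.841 with 30 analysed, 0.812 with 28, 0.795 with 27 and 0.740 with 24.

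The article gives no rate of related events, so no expected number of withdrawals is computed.

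**The case against.** The strongest reply is that {22} is loosely worded. Its examples are reasons to stop exercising, and the authors may have meant only that the patient leaves the sessions. Visits after discontinuation are also a detail that a condensed article commonly leaves to the full protocol. This stands in part: the silence on later visits is weak evidence, and the end of measurement must be put as a possibility. It does not remove the conflict between two stated rules. If only the sessions were meant, the sentence is wrong as written and the same edit corrects it.

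Other limits also stand.

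- A reader might infer that withdrawn patients are certain to be excluded under {20a}. Being unable to complete for uncontrollable reasons does not naturally describe removal by a protocol rule; it is one possible reading. The tension between that exclusion and the intention-to-treat analysis exists whatever {22} says.
- A reader might infer bias between the arms because only one receives ice. Both arms receive the same exergames dose and none of the examples in {22} is specific to ice, so the article does not show a difference. Nor does it show that there is none.
- A reader might treat 28 as a cliff. It is not: the fall from 0.812 at 28 to 0.795 at 27 is small.
- Section {22} expects low risk, and the Discussion says that few studies report adverse events with exergames, so few patients may be affected.
- The remaining benefit may be limited. The article appeared on 21 June 2024 and Trial status expects data collection to end by September 2024, whereas Recruitment {15} gives September 2024 as the end of recruitment. How many patients an amendment would still protect is unclear.

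**Conclusion.** The concern holds as an inconsistency that should be corrected. Sections {22} and {11b} prescribe different actions for severe related events and attributed side effects, and nothing reconciles them. That much rests on the text alone.

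The further consequence is conditional. If {22} is followed as worded and visits then stop, outcomes are lost because of harm, against the intention-to-treat analysis and the missing-data expectation in {20c}. Neither the size nor the direction of any resulting bias can be estimated from the article, and no figure is offered. The only firm scale is the two-patient margin in {14}, which all causes of loss share. The power figures rest on the assumed ρ = 0.5 and sphericity, and they show a modest cost in precision; the selective nature of the loss matters more.

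It would go too far to conclude that the article orders measurement to stop, or that a mandatory stop after events such as chest pain is itself a fault. A cautious stopping rule for the intervention is reasonable; safety does not require measurement to end with it.

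**What to change.** 1. In {22}, replace withdrawal from the trial with stopping the intervention. The clinicians may keep a mandatory stop for events such as chest pain or dyspnea. Align {11b} so that both sections give the same trigger and the same action.
2. State that stopping the intervention is not leaving the trial. Unless consent is withdrawn, the week-4 and week-12 measurements, flare counts and adverse-event follow-up continue, and the patient is analysed in the group to which he or she was randomised.
3. In {20a}, limit the exclusion of patients who do not complete to the per-protocol analysis, so that it cannot contradict the new text or the intention-to-treat analysis in {20c}.

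The cost is one amendment by the route in section {25} ("All revisions to the protocol require approval from the Human Research Ethics Committee at USM"), with notice to participants and researchers and a registry update, plus assessment visits for the patients who stop the sessions. Measurements of patients already withdrawn under the present wording may not be recoverable; their number and reasons should be reported.

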### Frequency and plans for auditing trial conduct {23}

An independent data monitoring committee, separate from the investigators and sponsors, will conduct audits of the trial at the 25%, 50%, and 75% stages of trial progression.

### Plans for communicating important protocol amendments to relevant parties (e.g., trial participants, ethical committees) {25}

All revisions to the protocol require approval from the Human Research Ethics Committee at USM. Once the revised protocol is approved, we will inform the participants and the involved researchers. We will also revise and update the protocol in the clinical trial registry. Any deviations from the protocol will be fully documented using a breach report form and submitted to Human Research Ethics Committee at USM.

### Dissemination plans {31a}

The results of this study will be published in an international, peer-reviewed journal, and the raw data will also be made publicly available through publication on an open data repository. Moreover, the results of the study will be reported in the Chinese Clinical Trial Registry and disseminated through patient and stakeholder workshops as well as relevant international conferences.

## Discussion

According to Jablonski et al. [9], low- to moderate-intensity exercise prevents inflammatory responses and decreased tissue swelling in a mouse model of acute gout. A cohort study conducted by McCormick et al. [22] indicates that addressing obesity is key for men with gout to benefit from other gout management approaches; obesity is also an internationally recognized modifiable risk factor for recurrent gout attacks [7]. Therefore, maintaining a non-obese weight and losing weight is a key factor in gout treatment [23].

It is generally acknowledged that neglecting exercise is one of the most prominent risk factors for increased BMI [24]. Personalized exercise rehabilitation interventions are effective for weight loss [8]. According to Nishida et al. [25], moderate-intensity exercise exhibited a negative correlation with serum uric acid levels in obese Japanese men. A large cross-sectional study based on the National Health and Nutrition Examination Survey (NHANES) in the United States demonstrated a non-linear relationship between exercise and SUA levels [26].

The British Society for Rheumatology Guideline for the Management of Gout suggests that ice could be an adjunct to acute gout treatment as it could effectively reduce pain in gout patients [1]. Schlesinger et al. [27] conducted a study to evaluate the effect of topical ice therapy on patients suffering from acute gout. The research result indicates that ice therapy significantly reduces pain. The application of post-exercise ice therapy can reduce tissue temperature and blood flow, thereby alleviating cardiovascular stress, eliminating muscle metabolic by-products, reducing exercise-induced symptoms, and accelerating post-exercise recovery [28]. Numerous studies have shown that ice therapy can effectively relieve DOMS at 24 h after exercise [29–33].

Exergames technology has been widely recognized in rehabilitation and has achieved positive results [34]. Fitness games used for therapeutic purposes, also known as serious games, can provide patients with an immersive experience that allows them to focus on training and achieve more optimal results in challenging and competitive programs [35]. Exergames typically provide light to moderate exercise training to help users burn calories. Studies have demonstrated the beneficial effects of exergames as an aid in weight loss [36]. Moreover, few studies report adverse events in exergames, and the safety of exergames is widely recognized [37]. However, the long-term effects of exergames need to be supplemented and verified by future research [36].

To our knowledge, no study has investigated the effect of exergames and ice therapy among gout patients. However, research evidence supports that exergames can improve persistence and significantly reduce BMI. Ice therapy can increase the patient’s adherence to exercise by reducing symptoms and joint responses after exercise, thereby assisting in better reducing BMI. Therefore, this study aims to examine the combined effect of exergames and ice therapy in patients with gout in Pulau Pinang. This study is expected to demonstrate that exergames combined with ice therapy are more effective in gout management compared to exergames alone. The outcome of this study could be used as guidelines for choosing the right exercise program to improve the health status of the gout population. This study would also benefit patients with gout by highlighting any gaps between their awareness and the correct concepts of gout management, encouraging them to prioritize exercise. The findings of this study may help healthcare practitioners re-evaluate gout treatments to identify and address deficiencies in current approaches to gout management, and establish a new program and perspective for gout management.

However, this study has some major scopes. Since no studies have reported the optimal exercise intensity and frequency for patients with gout, this study does not account for the potential effects of different intensities and frequencies of exercise. Moreover, as this study only included patients from Pulau Pinang, the findings may lack universality.

